### Discontinuation and Withdrawal of Participants From Study Treatment

Participants may withdraw at any point in either the qualitative or quantitative aspects of the study.

### Definition of End of Study

The end of study is the date of the last qualitative interview of the last participant.

### Procedure for Dealing with Missing, Unused, and Spurious Data

All data collected will be included in the analysis.

### Procedures for Reporting Any Deviation(s) From the Original Statistical Analysis Plan

The study will analyze observational data retrospectively, and so we do not anticipate any significant deviations as would be expected in a longitudinal study.

### Interim Analysis and Criteria for Early Study Termination

No interim analyses will be performed.

### Dissemination

Patient volunteers and patients who have taken part in the qualitative interviews will be invited to help with dissemination events. The results will be submitted for presentation at national conferences. There will also be reports on the Wessex Asthma Network website for patients and public to access [12]. All study participants will be given a summary of the study results in an appropriate format.

## Results

### Quantitative

The MISSION team screened GP records to identify uncontrolled asthmatics to invite to MISSION clinics. There were 369 patients identified who had one or more of the criteria that suggest uncontrolled or potentially severe asthma (high inhaled corticosteroid dose >500 mcg BDP (Beclomethasone Diproprionate) , 2 or more exacerbations in the last 12 months requiring steroids for more than 3 days, any hospital, ED or OOH contact in the last 12 months, and high SABA usage—>6 inhalers in the last 12 months or reduced lung function FEV1 ≤70%). All patients who were identified were approached for the MISSION project.

### Modern Innovative Solutions to Improve Outcomes in Rapid Access Asthma Clinic Patients and Severe Asthma Assessment Clinic Patients

The MISSION service: The searches identified 1436 patients who were manually reviewed by the MISSION team and 460 patients met the criteria. All these patients were invited to the clinic; 125 were booked in, and 84 attended the RAACs, of whom 22 were identified for the SAACs.

### Primary Care Patients

All patients identified by the GP search but who did not attend the MISSION clinics will be approached for the study to maximize the chance of getting the same number of participants to the number who consents from the MISSION group.

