### Sample Size

The study was powered to show a difference between the MISSION group and the primary care group for the primary outcome, exacerbation frequency. The sample size was based on an analysis of covariance (ANCOVA) approach, with the outcome being exacerbation frequency in the second 6-month period and with the exacerbation frequency in the first 6-month period being the covariate. Baseline data suggest a mean number of exacerbations for this group of 1.29, with an SD of 1.30. There is expected to be no change in exacerbation frequency between time periods for the primary care group, whereas it is anticipated that exacerbations in the MISSION group may reduce by 50% to 0.65 exacerbations. A correlation between the exacerbation rates in the 2 time periods of 0.5 is assumed. The primary care group will be larger, with an anticipated 3:1 ratio. To show a difference between groups with a 5% significance level and 90% power, it is calculated that 44 subjects in the MISSION group and 132 in the primary group are required.

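### The 90% power rests on three primary care controls per MISSION patient, but the stated recruitment aim is one per patient; the two targets conflict and should be reconciled

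*Protocol article*

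**What the plan says.** The Sample Size section of the protocol article bases the calculation on the MISSION versus primary care comparison of exacerbation frequency, analysed by ANCOVA. It states: "The primary care group will be larger, with an anticipated 3:1 ratio". It concludes that "44 subjects in the MISSION group and 132 in the primary group are required".

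Under Results, the Primary Care Patients section describes how that control group will be obtained. Everyone found by the GP search who did not attend is to be approached, and the purpose given is "to maximize the chance of getting the same number of participants to the number who consents from the MISSION group".

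The size of the pool is given twice under Results. The Quantitative section says "There were 369 patients identified who had one or more of the criteria" and that all of them were approached. The section on Rapid Access Asthma Clinic (RAAC) and Severe Asthma Assessment Clinic patients says "460 patients met the criteria", that all were invited, and that 84 attended the RAACs.

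**The concern.** Both sections concern the same control group in the comparison on which the study was powered. One requires three controls per MISSION patient. The other names equality with the MISSION consent count as the thing to be achieved. At the stated 44 MISSION patients, equality would supply one third of the required controls. The article does not reconcile the two and gives no power for a 1:1 comparison.

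At stake is how the result is read. If the control group ended near parity and the MISSION group near 44, a null finding could be presented as coming from a study with 90% power when its power was about 75%. As written, a reader cannot tell whether a parity sample would count as meeting the plan.

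The two pool sizes raise a smaller, separate question: which count is the denominator for the control group's response rate, and what consent rate is needed to reach 132.

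**Working it through.** **Inputs (Sample Size section).** "Baseline data suggest a mean number of exacerbations for this group of 1.29, with an SD of 1.30"; no change is expected in primary care; "exacerbations in the MISSION group may reduce by 50% to 0.65 exacerbations"; correlation between periods 0.5; 5% significance and 90% power. Sidedness is not stated. Two-sided is assumed because it reproduces the plan's figure, whereas one-sided gives 36 MISSION patients. No dropout inflation is stated, and none is needed to reproduce the figure.

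**Step 1: reproduce the plan's figure.**
- Difference: 1.29 − 0.65 = 0.64.
- ANCOVA residual variance: 1.30² × (1 − 0.5²) = 1.69 × 0.75 = 1.2675, so the residual SD is 1.126.
- MISSION n at 3:1: (1.960 + 1.282)² × 1.2675 × (1 + 1/3) / 0.64² = 43.35, rounded up to 44; 3 × 44 = 132.
- Power at 44 and 132: 90.4% (normal) or 90.1% (noncentral t, df = N − 3).

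The plan's arithmetic is therefore correct, and the 3:1 ratio is built into it. The unrounded difference of 0.645 gives 43 and 129, which is immaterial.

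**Step 2: size needed at 1:1 for 90%.** The variance factor at 44 and 132 is 1/44 + 1/132 = 4/132 = 1/33. Equal groups match this when 2/n = 1/33, so n = 66. The normal approximation gives 66 per group; noncentral t gives 89.99% at 66, so strictly 67.

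**Step 3: power if exact parity resulted.** Noncentrality is 0.64 / (1.126 × √(2/n)).

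| Per group | Power (noncentral t) | Share of the 84 RAAC attenders |
|---|---|---|
| 44 | 75.1% (normal 76.0%) | 52% |
| 55 | 84% | 65% |
| 66 | 89.99% | 79% |
| 67 | just over 90% | 80% |
| 84 | 95.6% | 100% |

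**Step 4: control consent rate needed for 132.**
- From the section that reports both the invitations and the attendance: 460 − 84 = 376 non-attenders; 132/376 = 35%.
- If 369 is the right count and the same 84 attended, which is an assumption because the article does not link those two figures: 369 − 84 = 285; 132/285 = 46%.

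**The case against.** A reader might infer that the study will stop seeking controls at parity and so has only about 75% power. The documents do not support that.

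First, the Primary Care Patients section approaches every non-attender, and the Quantitative part of Screening and Enrollment likewise approaches all primary care patients for consent. Parity appears as the reason for approaching everyone, not as a ceiling. Where the authors want recruitment to end at a number, they say so: the Outpatient Severe Asthma Patients section includes new referrals only until its sample size is met. No such rule is attached to the primary care group.

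Second, parity is tied to however many MISSION patients consent, not to 44. With 84 RAAC attenders, 44 is a required minimum, and the article gives no consent figure. The 75% is one scenario in a range that reaches about 96%.

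Third, the 369 versus 460 mismatch does not enter the power calculation, and the pool of 285 depends on combining counts from two sections.

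All three points stand, and they limit the consequence. They do not remove the inconsistency. Approaching everyone is a method; the aim attached to it is still equality, and at 44 MISSION patients that is 88 controls short of the number described as required.

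**Conclusion.** The point holds as an internal inconsistency in the control-group target for the primary comparison. The sample size calculation itself is right, and no shortfall is shown.

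If parity, and no more, were reached, power would run from about 75% at 44 per group to about 96% at 84. It would pass 90% only once 66 to 67 MISSION patients (79 to 80% of attenders) had consented, each matched in number by a control. If 44 MISSION and 132 primary care patients consent, the stated 90% stands.

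These figures rest on the plan's own mean, SD, effect and correlation, and on a two-sided 5% test.

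The two counts of patients meeting the criteria are a separate reporting discrepancy that adds no weight to the power point. It should be corrected because that count defines the control sampling frame.

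This should be fixed, but it does not by itself invalidate the design.

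**What to change.** Choose one target and state it in both places.

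- **If 3:1 is intended:** in the Primary Care Patients section under Results, replace the equal-numbers aim with at least 132 primary care patients (three per MISSION patient at 44), and say that recruitment does not stop at parity.
- **If parity is the real expectation:** restate the Sample Size section for 1:1, giving either about 75% power at 44 per group or about 67 per group for 90%.

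Separately, reconcile 369 with 460 under Results, or explain how the two counts differ, and state the resulting number of non-attenders.

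The cost is wording only. All non-attenders are already to be approached, so the 3:1 aim needs no new recruitment route.

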### Outpatient Severe Asthma Patients

The severe asthma outpatient clinic at Portsmouth Hospitals NHS Trust sees 16 new referrals per month. The sample will be matched to the same as the number of patients attending the SAACs, that is, 20 patients. All new referrals to the asthma clinic who meet the inclusion criteria will be included until the sample size is reached.

### Qualitative

All 20 patients from the MISSION SAACs will be approached for a qualitative interview. Furthermore, all clinical staff who attended the MISSION RAACs or SAACs will be approached for an interview with an anticipated number of 10 interviewed from primary care and 10 from secondary care.

## Discussion

The clinical intervention has been performed and the study has been ethically approved by the Yorkshire & The Humber-Leeds East Research Ethics Committee (Reference 15/YH/0136) and sponsored by Portsmouth Hospitals NHS Trust. The results will be reported in February 2020.

## Appendix

Multimedia Appendix 1 The study flow chart showing participants’ journey.

Multimedia Appendix 2 The case record form used for the Modern Innovative Solutions to Improve Outcomes Severe Asthma Assessment Clinics.

## Abbreviations

ACQ: Asthma Control Questionnaire
ANCOVA: analysis of covariance
AQLQ: Asthma Quality of Life Questionnaire
CT: computed tomography
ED: emergency department
ENT: ear, nose, and throat
FeNO: fractional exhaled nitric oxide
FEV1: forced expiratory volume in 1 second
FVC: forced vital capacity
GP: general practitioner
MDT: multidisciplinary team
MISSION: Modern Innovative Solutions to Improve Outcomes
NHS: National Health Service
OOH: out-of-hour
PIS: patient information sheet
RAAC: Rapid Access Asthma Clinic
RCT: randomized controlled trial
SAAC: Severe Asthma Assessment Clinic
SABA: short-acting beta-agonist
